## 2. Materials and Methods

### 2.1. Research Design

The ABA single-case experimental design will be used for the purpose of the study, as explained previously.

The research method is divided into three phases: an “A” baseline period of two weeks between the assessment session “0” and initial psychotherapy session; a “B” intervention period of minimum eight GT sessions; an “A” follow-up period of six months after the end of the intervention, with measurements at the final session, after two weeks and six months. More specifically, in relation to data collection, the following will happen in each phase: A—at the baseline, outcome measures will be administered at session “0”, and individual target complaints (TC) will be recorded daily for the following two weeks; B—in the intervention phase, target complaints will be completed daily; A—in the follow-up phase, participants will continue with daily assessment for another two weeks, while outcome measures will be administered at the final session, i.e., week two and week twenty-four (Figure 1).

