### 1.5. Proposed Research Aims and Objectives

The general objective of the research is to determine whether or not GT is an effective treatment for depression in PWD.

Specific objectives of the study are:-To assess if there is a pre/post improvement and, if so, how great this is (clinical significance), according to the outcome variables rates, as well as whether it can be attributed to the therapy intervention.-To assess if study participants suffer with loneliness.-To assess if loneliness is mitigated by the regular contact with the therapist.-To assess if the regular contact with the therapist affects the level of depression.-To assess if a clinical improvement of depression symptoms has an indirect effect on the level of family carers’ burden.-To assess if a clinical improvement has an indirect effect on the mutuality of the relationship between the patient and the family carer.

In order to achieve the objectives, the following research questions will need to be answered:Is there any pre/post treatment improvement?If the answer to question 1 is yes, is the change clinically significant (reduction of symptoms by 50%)?If loneliness is a factor, is the improvement solely due to the social contact with the therapist? ORCan the improvement be attributed to the therapy intervention?Can the improvement of the patient also have an impact on the caregiver’s burden and level of mutuality?

The researchers hypothesised that: depressive symptoms will improve post GT treatment and the improvement will be maintained at follow-up; the level of loneliness, if a factor, can decrease post-treatment and remain so at follow-up; the improvement of symptoms is related to the GT treatment; the level of burden of the family carer will reduce whilst the mutuality in the relationship will increase as the PWD’s depression improves.

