### 2.4. Measures and Data Collection Tools

Overall, data will be collected through questionnaires and audio/video recording. Outcome measures will gather quantitative data on the symptoms, quality of life, level of loneliness, family carers’ burden, and mutuality and will be administered at session “0”, at the final session and follow-up (week 2 and week 24), whilst target complaints will be repeated daily and used for the time series analysis. All the measures and related administration time points are shown in Table 1 and described below.

The Neuropsychiatric Inventory Questionnaire (NPI) was developed by Cummings et al. [73] and validated by Binetti et al. [74] for the Italian population and by Zepeda et al. [75] for the Mexican population. It measures the behavioural symptoms related to dementia conditions, assessing twelve sub-domains: delusions, hallucinations, agitation/aggression, depression/dysphoria, anxiety, elation/euphoria, apathy/indifference, disinhibition, irritability/lability, motor disturbance, night-time behaviours, and appetite/eating. Additionally, a caregiver distress scale was included for measuring the psychological impact of the neuropsychiatric symptoms on family caregivers [76]. The NPI anxiety (NPI-A) score will be used to assess the level of anxiety of participants at pre/post treatment. The test has good internal consistency, content validity, and inter-rater/test-retest reliability.

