### 2.5. Data Analysis

Continuous variables will be analysed and reported as mean ± SD (standard deviation) or median and IQR (interquartile range), on the basis of their distribution (assessed through Shapiro–Wilk test). Discrete variables will be reported as absolute frequencies and percentage.

In order to evaluate any pre/post improvements (from baseline to follow-up: at the final session, after two weeks and twenty-four weeks following the end of the treatment) in the main outcomes, i.e., depression and anxiety symptoms (GDS; NPI-A), quality of life (QOL-AD), and the therapy outcome (CORE–OM), three types of analysis will be carried out: (a) visual analysis, comparing the target complaint (TC) scores during the three phases; (b) mean difference from baseline to follow-up tested, by means of paired t-test or Mann–Whitney U test, according to the distribution of the outcome variable [99]; (c) mean baseline reduction (MBLR) for obtaining the effect size for single-case designs [100,101,102], as follows:MBLR = (Mean of Baseline phase − Mean of Follow-up phase) × 100/Mean of Baseline phase.(1)

The same procedure will be applied for the secondary outcome, i.e., loneliness. Additionally, data collected from family caregivers (i.e., QOL-AD family version, caregiver burden scale, and the mutuality scale) during the three phases of the study will be compared with subjects’ outcomes, in order to evaluate indirect effects of the treatment, by means of Pearson or Spearman correlation coefficients, as appropriate.

Blind raters will assess the fidelity of the approach by rating a small sample of sessions through the GTFS.

A two-tailed *p* value < 0.05 will be considered significant. Data will be analysed using SPSS for Windows V24.0 (SPSS Inc., Chicago, IL, USA) and Simulation Modeling Analysis (SMA) for Windows V07.30.20 (ClinicalResearcher, Jeff Borckardt, Medical University of South Carolina).

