## 3. Discussion

Depression in dementia can be treated with the use of psychosocial interventions, psychotherapy being part of this category. Any therapeutic approach that is used to work with PWD should be flexible, person-centred, and creative, in order to meet the needs of the person, as it has been well-underlined by Kitwood and followers [103,104]. These qualities are already central in GT and testify to the suitability of the approach for working with this population.

The design of this study mainly followed indications for the development of a SCED in GT, as recommended by GT authors with experience in research [70,105]. The aim of observing the effectiveness of the approach has been enriched by considering the context of the experience of living with dementia, which inevitably includes informal carers, who are often family members. Therefore, the benefits of receiving GT as treatment should also be observed from the perspective of the main family carer. This added aspect is in line with the GT field principle, i.e., that the embodied learning from the therapeutic “dance” can elicit relational adaptations (a *new dance*) in the family system.

Providing psychotherapeutic support from the earliest stages of dementia allows the patients to cope with the disease from the very beginning, integrating it into their lives and becoming protagonists of the future therapeutic choices. A grieving reaction, accompanied by an emotional crisis, which may include depression, may be experienced from the moment of diagnosis [106], as a response to it, or even before diagnosis [107], as the person’s life begins to be affected by the initial symptoms of dementia. The support received through a psychotherapeutic intervention can help the person to cope with losses, in order to create continuous new adaptations. GT’s holistic approach makes it possible to undertake a pathway to support the physiological, emotional, and cognitive ground of the patient that may be disrupted by the dementia condition.

It is expected that the results obtained from this research can submit significant data to support the impact between pre/post improvement, as well as whether the observed changes are clinically significant. It will be possible to review the attribution of these changes to the Gestalt therapeutic work.

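### Maintained improvement is hypothesised, so the second A phase is expected to show no reversal; with one fixed baseline and one pre-therapy GDS, the design supports improvement over time rather than attribution to Gestalt therapy

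*Protocol article*

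**What the plan says.** **Question.** Section 1.5 of the Protocol article sets out to assess improvement "as well as whether it can be attributed to the therapy intervention". It names a rival explanation: "is the improvement solely due to the social contact with the therapist". The Discussion (section 3) expects that "It will be possible to review the attribution of these changes to the Gestalt therapeutic work".

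**Hypothesis.** Section 1.5 predicts that "depressive symptoms will improve post GT treatment and the improvement will be maintained at follow-up".

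**Design.** Section 2.1: "The ABA single-case experimental design will be used for the purpose of the study". The first A phase is a "baseline period of two weeks between the assessment session" and the first therapy session, the same for every participant. B is at least eight weekly sessions. The second A is a six-month follow-up. No randomised or planned staggered start, second B phase or contact-only phase is described.

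**Measurement.** The GDS and the other outcome measures are given once before therapy, at session 0, and then "at the final session and follow-up (week 2 and week 24") (section 2.4; Table 1 agrees). Target complaints (TC) are rated daily, which gives about 14 baseline ratings.

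**Analysis.** Section 2.5 lists "visual analysis, comparing the target complaint (TC) scores during the three phases", a baseline-to-follow-up mean test, and the mean baseline reduction (MBLR), which also compares baseline with follow-up. The abstract and section 2.4 speak of time series analysis, and section 2.5 names the Simulation Modeling Analysis (SMA) software.

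**The concern.** In an ABA design the within-person evidence for causation is withdrawal: the outcome changes when treatment starts and goes back when it stops. A plan that expects the gain to persist does not expect that evidence. The design then works as A-B, with one phase change per person.

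A single A-B change at the same point for everyone leaves time as a competing explanation, whether through spontaneous remission, adjustment after diagnosis or any other drift following study entry. Twelve repetitions do not remove it, because such drift would move all participants in the same direction at the same stage. The GDS is weaker still: one pre-therapy value gives no untreated interval, and for those who qualify on the 10–19 window it carries some regression to the mean. MBLR and the mean test compare only the ends of the study and so cannot locate a change at the start of therapy.

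At stake is a stated research question. The study could report attribution to Gestalt therapy (GT) when its data show only that participants were better later than earlier.

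**Working it through.** **1. The plan's own figure.** The sample size of 12 comes from 4–10 cases plus 20–30% dropout. 10 × 1.2 = 12 reproduces it (10/0.8 = 12.5, rounded up to 13, is close). Completers would be 12 × 0.8 = 9.6 or 12 × 0.7 = 8.4, so 9 is used below. No effect size or power is stated, and the point does not depend on 12.

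**2. What the second A phase can show.**

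| Outcome in second A | Maintenance hypothesis | Reversal evidence |
|---|---|---|
| Gain kept | upheld | none |
| Return towards baseline | fails | present |

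The predicted row is the first: the expected difference between B and second A is zero. Even the second row would not separate GT from therapist contact, because both stop together.

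**3. Whether a time series test separates therapy from time.** Simulation on assumed values: 14 days of A, 56 days of B (eight weekly sessions), no therapy effect, and a straight-line improvement over the 70 days in units of the day-to-day SD. The A-versus-B level test used a threshold adjusted for the lag-1 autocorrelation. Proportion of cases significant at 0.05:

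| Lag-1 autocorrelation | No drift | 1 SD drift | 2 SD drift |
|---|---|---|---|
| 0 | 5% | 40% | 93% |
| 0.4 | 5% | 20% | 64% |
| 0.6 | 5% | 16% | 46% |

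The test is valid when nothing drifts. When something does, a level test reports it as a phase effect. A slope term helps only as far as the baseline can show the trend. With effective n = n/(1 + 2Σ(1 − k/n)ρ^k) and n = 14, the baseline is worth 7.9, 5.2 or 3.1 independent days at ρ = 0.3, 0.5 or 0.7 (assumed).

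**4. Regression to the mean in the GDS.** Simulation of true score plus error, selecting an observed baseline of 10–19, with no real change. Assumed: SD 6, test-retest reliability 0.70 or 0.85, source mean 8 to 14 (the documents give none of these for the GDS). Range over the two reliabilities:

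| Source mean | Mean fall (points) | MBLR | Paired t-test shows improvement, n = 9 |
|---|---|---|---|
| 8 | 0.78–1.56 | 5.9–11.8% | 9.7–15.4% |
| 10 | 0.54–1.07 | 4.0–7.9% | 6.5–9.4% |
| 12 | 0.29–0.60 | 2.0–4.3% | 4.0–5.5% |
| 14 | 0.06–0.12 | 0.4–0.8% | 2.7–3.0% |

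The nominal rate for improvement is 2.5%. The section 1.5 criterion for clinical significance is a 50% reduction, far above any MBLR here. A second pre-therapy GDS is not itself selected on, so with independent errors its average with the first halves the fall: 1.56/2 = 0.78 at most.

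**5. What randomised baseline lengths would add.** With one fixed start there is one possible assignment and no randomisation test. With three lengths (an assumed number), 12 participants and four per length, there are 12!/(4!4!4!) = 34,650. Stratified by country, six each and two per length, there are (6!/(2!2!2!))² = 90² = 8,100, so the smallest p-value is 1/8,100 ≈ 0.00012 before dropout.

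**The case against.** Several objections have force.

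- **Analysis.** A reader might infer from section 2.5 that attribution rests on looking at graphs. The documents do not support that: time series analysis is announced and SMA is named. The exact SMA contrast may properly sit in an analysis plan not shown here. This stands, but step 3 shows that software does not supply the missing control.
- **Target complaints.** A reader might infer that the daily ratings are uninformative. They are not. Section 2.3 requires constant psychotropic treatment and excludes parallel therapy, section 2.4 asks for complaints that stay stable if untreated, and there are about 14 baseline days and 12 replicates in two countries. A flat baseline followed by a shift at session 1 would not look like slow remission. This stands for TC; it does not help the GDS.
- **Regression to the mean.** A reader might infer that it could explain a positive result. It is small, nearly vanishes if the source mean is near 14, and applies less to participants who enter on anxiety alone, since the entry criterion is and/or. This stands.
- **Labelling.** Section 2.1 already calls the second A follow-up and nowhere says that attribution depends on reversal. This stands, but then no other feature of the design supplies experimental control.
- **Randomised starts.** A reader might infer that these would permit attribution to GT itself. They would not, because therapist contact starts and stops with GT.

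**Conclusion.** The point holds in a limited form. If the study's own hypothesis is right, the second A phase contributes no reversal evidence. For depression, one pre-therapy GDS and a uniform two-week baseline mean that change cannot be separated from the passage of time or from regression to the mean. The daily TC series can show a phase-linked shift, but only one per case at a fixed start.

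It does not follow that the attribution question is beyond reach in every respect, or that the planned TC analysis is only visual. The claim is that the design as written supports improvement over time, and that the wording of section 1.5 and the Discussion goes further.

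The sizes rest on assumptions. Drift of 1 to 2 SD over 70 days gives 16% to 93% false phase effects per case. Regression to the mean is 0.06 to 1.6 GDS points for source means of 8 to 14, SD 6 and reliability 0.70 to 0.85. The structural conclusion needs none of these values.

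This should be settled before enrolment, since neither a missed pre-therapy GDS nor a randomised start can be added later.

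**What to change.** 1. **Repeat the GDS just before session 1.** Use the two pre-therapy scores as the baseline, and their difference as a check on untreated change. Cost: one more 30-item questionnaire per participant. Limit: two weeks is short against at least eight weeks of therapy, so slow drift may not show.
2. **Rest any attribution statement on the autocorrelation-adjusted A-versus-B contrast of daily TC, in level and slope**, not on the baseline-to-follow-up contrast or on return to baseline. Treat the second A as maintenance follow-up throughout. Cost: wording; SMA is already named.
3. **Preferably randomise each participant's baseline length**, stratified by country, among lengths the clinical team accepts. Cost: some participants wait longer for session 1 and complete more daily forms.
4. **Match the conclusion to the design in section 1.5 and the Discussion.** Without item 3, limit it to improvement over time. With item 3, limit it to an effect of GT together with therapist contact, because no contact-only phase exists to separate them.

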### 2.2. Study Setting and Intervention

The intervention will consist of individual GT sessions, delivered weekly for the duration of one hour each. The minimum number of sessions is eight, whilst a maximum number will be recorded, depending on the individual needs of the participants with dementia.

The intervention will be delivered in psychotherapeutic settings, provided by public health clinics or private therapy centres.

Participants will be provided with an information sheet describing the study purpose and procedure, and they will be asked to sign a consent form for data collection and treatment. The full anonymity of the individuals taking part in the treatment will be ensured, according to the general data protection regulation (2016/679) [69] and national laws on the privacy of sensitive and health-related data, currently in force in Italy and in Mexico. The study protocol will be submitted to the attention of the competent ethics committees.

### 2.3. Sample and Recruitment

Recruitment will involve two groups of participants: 6 Gestalt psychotherapists and 12 PWD suffering from depression, with 6 in Italy and 6 in Mexico, respectively. The sample size has been chosen on the basis of recommendations provided for SCED in GT, which state that a number of 4 to 10 cases can give the study an international validation for the efficacy of the method for a specific type of problem [70]. For this research, the study number is slightly higher to include a dropout rate of 20–30%. In line with the above, the researchers decided to have as an inclusive approach as possible, with the twofold aim of giving a chance of treatment to patients with different types of dementia (i.e., for compassionate reasons) and observing its impact on them (i.e., for research interest).

To be part of the study, PWD will need to: (a) provide evidence of a formal diagnosis by a medical doctor, i.e., a neurologist, geriatrist, or psychiatrist; (b) have a clinical dementia rating–sum of the boxes (CDR-SOB) score of 3–4 (very mild dementia) or 4.5–9 (mild dementia) [71]; (c) be able to engage in therapy; (d) display symptoms of mild depression, i.e., geriatric depression scale (GDS) score 10–19 [72] and/or anxiety (neuropsychiatric inventory anxiety subscale, NPI-A score ≥ 4 [73]); (e) maintain the psychopharmacological treatment during the investigation; f) live in the community.

Exclusion criteria are: (a) diagnosis/symptoms of dementia at a moderate–severe stage (given by a medical specialist) or CDR-SOB score of 9.5–18; (b) display of challenging behaviours, delusions, or psychotic symptoms or major depression (GDS score between 20–30); (c) high level of risk and safeguarding issues; (d) parallel therapy/intervention for the same target complaint (e.g., psychoeducational groups); (e) variation in psychopharmacological treatment during the investigation; (f) admission to hospital/residential care.

Gestalt psychotherapists included will need to: (a) agree to participate, be recorded during sessions, and fill in questionnaires; (b) be state licensed Gestalt psychotherapists, with previous experience of working with PWD; (c) have access to supervision with a Gestalt supervisor.

PWD will be recruited through public health clinics in Italy and Mexico. The research team will contact health centres with a request to inform eligible patients (according to the judgement of their specialist doctor) about the study; possible participants can then contact the team themselves or agree to have their contact information forwarded to the researcher. Recruitment will be carried out by Gestalt psychotherapists, who are also clinical psychologists with experience in the field of neuropsychology and dementia. Gestalt psychotherapists will be recruited through national professional bodies and organizations.

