## Abstract

Psychotherapy is one of the evidence-based clinical interventions for the treatment of depression in older adults with dementia. Randomised controlled trials are often the first methodological choice to gain evidence, yet they are not applicable to a wide range of humanistic psychotherapies. Amongst all, the efficacy of the Gestalt therapy (GT) is under-investigated. The purpose of this paper is to present a research protocol, aiming to assess the effects of a GT-based intervention on people with dementia (PWD) and indirect influence on their family carers. The study implements the single-case experimental design with time series analysis that will be carried out in Italy and Mexico. Six people in each country, who received a diagnosis of dementia and present depressive symptoms, will be recruited. Eight or more GT sessions will be provided, whose fidelity will be assessed by the GT fidelity scale. Quantitative outcome measures are foreseen for monitoring participants’ depression, anxiety, quality of life, loneliness, carers’ burden, and the caregiving dyad mutuality at baseline and follow-up. The advantages and limitations of the research design are considered. If GT will effectively result in the treatment of depression in PWD, it could enrich the range of evidence-based interventions provided by healthcare services.

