### 1.2. The Contest of Dementia Diagnosis and Formal Care: A Snapshot of Italy and Mexico

The care and the management of dementia differs country-by-country, depending on epidemiological figures, the long-term care (LCT) system, welfare regimes, and level of country income. In Latin America, the prevalence of diagnosed dementia in 2010 was 3.10 million cases, compared to 9.95 million in Europe, and an increase of 393% is expected by 2050, compared to an 87% rise in Europe [36]. The increasing number of diagnosed PWD will contribute to growing inequalities in low- and middle-income countries, where 15% of dementia-related costs is covered by social care, compared to 40% in high-income countries [37].

Despite Europe being considered a wealthy continent with a better health system, compared to Latin America, the quality and level of care provided to PWD, from the time of diagnosis onwards, can differ significantly in each country.

This article shows an intervention research protocol, targeted to PWD and depressive symptoms living in Mexico and in Italy. Since these countries have different LTC systems and gross domestic products (GDP), the epidemiological and socio-economic contexts have been explored and are described in the following sub-paragraphs, in order to provide the rationale of the study protocol presented in this paper.

In Italy, the overall number of PWD will almost double from 2018 to 2050, reaching the figure of 2,247,715 individuals, which will represent 4.13% of the overall population, compared to 2.12% in 2018 [38,39], thus keeping in line with the European and western world trend. In the country, diagnosis of dementia is frequently made in hospital, when the person is at a middle-advanced stage of the illness, contrary to what happens in other European countries, such as the United Kingdom, where health services promote early diagnosis, and memory services have a great focus on providing support at the early stages of the disease. Although the intent is to slow down the progress of the disease, in Italy, there is neither a clear strategy to facilitate early diagnosis nor to promote a person-centred care aimed at keeping the person independent and cutting the cost of LTC. The diagnosis of dementia is often not even communicated to the patients, but only to their family members, and working on acceptance of the new condition can be problematic.

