The clinical dementia rating (CDR) is a multidimensional tool that measures the level of cognitive and functional impairment from the patient and proxy point of view. The information is collected by independent semi-structured interviews. Assessed domains include: memory, orientation, judgment and problem solving, community affairs, home and hobbies, and personal care. The score ranges from no impairment to severe dementia on a five-point scale. For the purpose of this project, the “sum of the boxes” (SOB) scoring method will be used: each domain box scores are summed, giving the possibility to differentiate between very mild (3–4) and mild dementia (4.5–9). CDR is widely used in research for its well-established validity and reliability [77,78]; additionally, the CDR-SOB method gained good reliability [71,79] and reputable use of its indexes of severity in therapeutic trials [80]. In this research, CDR will be used to assess the level of dementia at the recruitment phase, then to observe any natural progression of dementia, as a confounded variable at follow-up.

The geriatric depression scale (GDS) is a screening tool consisting of a 30-item questionnaire for measuring symptoms of depression in older people. Its cut-off score is 9/30 and mild depression ranges between 10–19, whilst severe depression between 20–30. It is widely used in research and clinical settings because of its sensitivity (92%) and specificity (89%). GDS seems reliable to detect depression in mild-to-moderate dementia, depending on the level of insight of the person; therefore, it needs caution in administration [72].

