The target complaints (TC) daily form [81] is a co-constructed self-report measure of three central idiosyncratic issues and one general wellbeing item. The items are identified together with the therapist at session “0”, then rated daily on a Likert-scale, from 1 to 10, where 1 equals “not bothered at all” and 10 equals “could not be worse”. Each complaint should be concrete, measurable/quantifiable, frequent, stable without treatment, relatively independent from one another, specific, and negatively formulated. The main instruction that helps identifying and scoring the target complaints is “Please record up to three presenting concerns that brought you to therapy. Circle the number that best represents your personal degree of discomfort as a result of each issue.” Improvement on global assessments and target complaints correlated at 0.71 [82], and test-retest reliability was at 0.76 [83].

The University of California, Los Angeles loneliness scale version 3 (UCLA-LS3) is a 20-item, self-reported questionnaire, broadly used to measure subjective feelings of loneliness and social isolation in various populations, including older adults and people with dementia. UCLA-LS3 has a well-established validity and reliability for its use in different languages, among which are Italian and Spanish [84,85,86]. The scale will be used to assess whether loneliness is a present factor and to observe whether regular contact with the therapist, rather than treatment, can influence this secondary variable and, thus, the level of depression (primary variable).

The quality of life-Alzheimer’s disease (QOL-AD) is a self-report tool for the PWD and their proxy/caregiver, based on 13 items of multiple domains, including physical health, mood, marriage, and fun. QOL-AD has excellent internal consistency and inter-rater reliability, as well as good criterion and construct validity [87].

The Ad-hoc common assessment tool is a questionnaire aimed at obtaining information on the level of care required by the PWD. It is an idiosyncratic and non-standardised tool, containing questions such as the weekly hours of caregiving and type of formal or informal support involved.

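### Inclusion criterion (d) admits people below the protocol's own depression cut-off on anxiety alone, which contradicts the stated depressed sample and weakens the pooled GDS results

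*Protocol article*

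**What the plan says.** **Who is to be recruited.** Section 2.3 gives the sample as "12 PWD suffering from depression, with 6 in Italy and 6 in Mexico". The abstract describes people "who received a diagnosis of dementia and present depressive symptoms, will be recruited". Section 1.2 calls the intervention "targeted to PWD and depressive symptoms living in Mexico and in Italy".

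**What the study is for.** The general objective in section 1.5 is to "determine whether or not GT is an effective treatment for depression in PWD". In the loneliness-scale paragraph of section 2.4, depression is the primary variable: "influence this secondary variable and, thus, the level of depression (primary variable".

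**Who is eligible.** Criterion (d) in section 2.3 asks for symptoms of mild depression and/or anxiety, defined as "GDS) score 10–19 [72] and/or anxiety (neuropsychiatric inventory anxiety subscale, NPI-A score ≥ 4". No other inclusion criterion sets a lower GDS limit. The only GDS-based exclusion is a score of 20–30.

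**How the scale is read.** Section 2.4 says of the GDS: "Its cut-off score is 9/30 and mild depression ranges between 10–19, whilst severe depression between 20–30".

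**How the scale is analysed.** Section 2.5 lists GDS and NPI-A together among the main outcomes, with QOL-AD and CORE–OM. It plans a visual analysis of target complaints, a test of the mean difference from baseline to follow-up, and MBLR. It does not separate participants by the criterion through which they entered. Section 1.5 sets clinical significance at a 50% reduction of symptoms.

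**The concern.** The population that the article describes and the population that its criterion admits are not the same. A participant who enters on anxiety with GDS 0–9 lies in no depression band that the protocol recognises. That person has little room to improve on GDS and cannot show whether the therapy treats depression.

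Three results bear directly on the general objective: the pre/post test on GDS, the GDS MBLR, and the 50% question if it is put to GDS. In a study of 12, a handful of such entrants can visibly move all three. The sample-size rationale also rests on 4 to 10 cases of one specific type of problem, so each anxiety-only entrant reduces the number of cases that count towards it.

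**Working it through.** **1. Eligibility by GDS score, for a person with NPI-A of 4 or more (sections 2.3 and 2.4)**

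| GDS at session 0 | Band in section 2.4 | Meets (d)? | Excluded on GDS? | Result |
|---|---|---|---|---|
| 0–9 | not above the cut-off | yes, through anxiety | no | eligible |
| 10–19 | mild depression | yes | no | eligible |
| 20–30 | severe depression | yes, through anxiety | yes | not eligible |

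The first row is the conflict. It follows from the wording alone.

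**2. The planned number.** Twelve is a rule-of-thumb figure (4 to 10 cases, raised for 20–30% dropout), not the result of a power calculation. It can be recovered: 8/(1 − 0.30) = 11.4 and 9/(1 − 0.20) = 11.25, both rounding up to 12. In reverse, 12 × 0.8 = 9.6 and 12 × 0.7 = 8.4 completers, inside the 4–10 range. With 3 anxiety-only entrants, 9 depressed participants remain before dropout, and 9 × 0.7 = 6.3 to 9 × 0.8 = 7.2 after it.

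**3. Where the GDS results are pooled.** GDS is taken once before treatment and at three points from the final session on. With one baseline value per person, a test of mean pre/post difference can only run across participants. Daily target complaints are analysed within a person and do not depend on anyone else's GDS.

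**4. Effect on MBLR (illustration).** Formula from section 2.5: MBLR = (baseline mean − follow-up mean) × 100 / baseline mean. Assumptions not in the document: depressed entrants start at 14.5 (middle of 10–19) and fall by 50%, or 7.25 points; anxiety-only entrants start at 4.5 (middle of 0–9) and do not change.

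| Anxiety-only of 12 | Baseline mean | Mean fall | Group MBLR |
|---|---|---|---|
| 0 | 14.5 | 7.25 | 50% |
| 3 | (9 × 14.5 + 3 × 4.5)/12 = 12.0 | 9 × 7.25/12 = 5.44 | 45% |
| 6 | (6 × 14.5 + 6 × 4.5)/12 = 9.5 | 6 × 7.25/12 = 3.63 | 38% |

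Every depressed participant reaches 50% in each row, yet the group figure falls below it.

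**5. Low baselines.** If the 50% rule is applied to individual GDS scores, a fall from 2 to 1 meets it with one point, while a start of 14 needs seven.

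**6. Effect on the pre/post test (illustration).** Paired t-test, n = 12, two-sided 0.05. Depressed entrants improve by an assumed 4 points with SD 5 (standardised change 0.8). Anxiety-only entrants change by 0 on average, with an SD of either 2 (simulated) or 5. The SD 5 case uses the noncentral t with standardised change 0.8(1 − f)/√(1 + f(1 − f) × 0.8²), where f is the anxiety-only share. For f = 3/12 this is 0.6/1.058 = 0.57.

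| Anxiety-only | Mean gain, all 12 | Power, all 12 (SD 2) | Power, all 12 (SD 5) | Power, depressed only |
|---|---|---|---|---|
| 0 | 4.0 | 71% | 71% | 71% (n = 12) |
| 3 | 3.0 | 52% | 43% | 56% (n = 9) |
| 4 | 2.7 | 43% | 35% | 50% (n = 8) |
| 6 | 2.0 | 26% | 22% | 36% (n = 6) |

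With a standardised change of 1.0 and equal spread, power on all 12 is 88%, 58%, 48% and 29% for 0, 3, 4 and 6 such entrants. The last column of the table shows that much of the loss comes from having fewer depressed participants, so restricting the analysis recovers only part of it.

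**The case against.** **Anxiety is itself a main outcome.** Section 2.5 lists NPI-A beside GDS, and Table 1 schedules it before and after treatment. Entry on either symptom is a coherent choice and probably explains the wording. This stands as an explanation, but it does not bring the criterion into line with the stated sample, the objective or the primary variable.

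**The inclusive approach is deliberate.** Section 2.3 does say so, but it ties this to different types of dementia, not to people below the depression cut-off.

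**This is a single-case design with no power claim.** This largely stands. Target complaints are chosen and rated by each person, and the sample size does not rest on power. The harm is confined to the pooled GDS summaries and the 50% question.

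**Stronger readings that the document does not support.** A reader might infer that the criterion admits people with no depressive symptoms. GDS 0–9 is not above the cut-off, which is not the same as symptom-free, and section 2.4 itself warns that the GDS depends on insight. A reader might also infer that the plan commits all 12 to the GDS test, or counts a fall from 2 to 1 as a response. Section 2.5 names no analysis set, which an article may leave to a fuller document, and section 1.5 ties the 50% rule to no particular scale. These are possible consequences, not stated rules.

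**Conclusion.** The contradiction holds on the wording alone: criterion (d) lets in people with GDS 0–9 on anxiety, while the sample description, abstract, general objective and primary variable all concern depression. As section 2.5 is written, nothing keeps such entrants out of the pooled GDS test and MBLR. They would pull the GDS change towards zero and blur any 50% reduction.

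The direction is clear if these entrants improve less on GDS than depressed entrants, as their limited room suggests. The size is not known, because the document gives neither their expected number nor the spread of GDS change. The MBLR and power figures are illustrations under assumptions and should not be read as estimates of actual harm. The within-person target-complaint results are little affected.

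**What to change.** Reconcile the passages before recruitment, by one of two routes.

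- **Require depression.** Make GDS 10–19 mandatory in criterion (d), with anxiety optional. This is a small change of wording and leaves the planned 12 as it is. The cost is somewhat narrower recruitment.
- **Keep anxiety-only entrants and say so.** Widen the stated population and objective in the abstract and sections 1.2, 1.5 and 2.3. Restrict GDS analyses, and any 50% criterion applied to GDS, to participants with GDS of 10 or more at session 0. The cost is fewer participants in those analyses. The estimate then answers the depression question, but little power may be regained: from 52% to 56% with three anxiety-only entrants in the SD 2 illustration, and from 43% to 56% in the SD 5 one, against 71% with none.

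Under either route, restrict NPI-A change analyses to those with NPI-A of 4 or more at session 0. NPI-A stays a main outcome, and depressed entrants with little anxiety would create the same floor problem there. This costs one sentence in section 2.5 and a smaller number in that analysis.
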